## Abstract

Gastrointestinal emergencies (GE) are frequently encountered in emergency department (ED), and patients can present with wide-ranging symptoms. more than 3 million patients admitted to US hospitals each year for EGS diagnoses, more than the sum of all new cancer diagnoses. In addition to the complexity of the urgent surgical patient (often suffering from multiple co-morbidities), there is the unpredictability and the severity of the event. In the light of this, these patients need a rapid decision-making process that allows a correct diagnosis and an adequate and timely treatment. The primary endpoint of this Italian nationwide study is to analyze the clinicopathological findings, management strategies and short-term outcomes of gastrointestinal emergency procedures performed in patients over 18. Secondary endpoints will be to evaluate to analyze the prognostic role of existing risk-scores to define the most suitable scoring system for gastro-intestinal surgical emergency. The primary outcomes are 30-day overall postoperative morbidity and mortality rates. Secondary outcomes are 30-day postoperative morbidity and mortality rates, stratified for each procedure or cause of intervention, length of hospital stay, admission and length of stay in ICU, and place of discharge (home or rehabilitation or care facility). In conclusion, to improve the level of care that should be reserved for these patients, we aim to analyze the clinicopathological findings, management strategies and short-term outcomes of gastrointestinal emergency procedures performed in patients over 18, to analyze the prognostic role of existing risk-scores and to define new tools suitable for EGS. This process could ameliorate outcomes and avoid futile treatments. These results may potentially influence the survival of many high-risk EGS procedure.

## Introduction

Gastrointestinal emergencies (GE) are frequently encountered in emergency department (ED), and patients can present with wide-ranging symptoms (1–4). Symptoms that suggest an underlying GE can include: abdominal pain; nausea; vomiting; diarrhea; melaena; hematemesis; constipation; jaundice; and abdominal distension. The acute abdomen (AA) is a term given to sudden severe pain in the abdomen requiring fast diagnosis and treatment usually requiring emergency surgical procedures (5–7). Causes of AA may include: appendicitis; pancreatitis; peptic ulcer disease (PUD); gall bladder pathology; intestinal ischemia; diverticulitis; intestinal obstruction; and ruptured ectopic pregnancy. Emergency gastrointestinal surgery (EGS) is burdened by significant mortality and morbidity rates because it is performed with little to no advance planning or preparation, on patients who are in dire straits (8–10). Scott JW et al report that there are more than 3 million patients admitted to US hospitals each year for EGS diagnoses, more than the sum of all new cancer diagnoses (11). In addition to the complexity of the urgent surgical patient (often suffering from multiple co-morbidities), there is the unpredictability and the severity of the event. Frequently, it is necessary a rapid decision-making that allows a correct diagnosis and an adequate and timely treatment (12–14). Moreover, in other study Havens JM et al report that patient undergoing EGS operation are up to 8 times more likely to die postoperatively than are patients undergoing the same procedures electively (15). Furthermore, the increase in average life will lead more and more people over 65 to face surgical pathologies in an emergency setting. EGS in the elderly is characterized by a greater morbidity and mortality as well as by a global worsening of the residual quality of life (QoL) (16, 17). The explanation for the high percentage of acute complications could be found in the inevitable reduction of the functional reserve related to the age. An example is the reduction of the body's immune defenses in the humoral response of B cells, in the cell-mediated immune function and macrophage activity which explains the susceptibility to infectious complications, facilitated by the altered integrity of the skin barrier and mucous membranes too (18, 19). Any tool that can help the surgeon in the decision making process, could become very useful in order to reduce mortality and morbidity linked to the EGS (20–22). To do this, it is necessary to study the greatest number of risk factors associated with EGS, considering all age groups and all type of diseases.

## Protocol

### Objectives

The primary endpoint of this Italian nationwide study is to analyze the clinicopathological findings, management strategies and short-term outcomes of gastrointestinal emergency procedures performed in patients over 18. Secondary endpoints will be to evaluate to analyze the prognostic role of existing risk-scores to define the most suitable scoring system for gastro-intestinal surgical emergency. We will conduct an epidemiological investigation to gather information about the number of patients operated on yearly, and the prevalence of various pathological conditions leading patients to need emergency surgery. Furthermore, we aim to identify any specific parameters that may be used as variables for new scoring system, peri-operative variables predicting adverse results and any critical issues in the management of these patients.

### Study design and participating sites

The prospective, observational study will be conducted following a resident-led model, similar to what has been described by Banghu et al. and van Rossem et al. and the SPIRIT guidelines (23–25). Briefly, teams of medical students and surgical residents with senior staff surgeon oversight collect data on patients across Italy for 18 months. The Data Coordination Center (DCC) is the Colorectal Surgery Unit of Surgery Centre, – Fondazione Campus Bio-Medico University Hospital, University Campus Bio-Medico of Rome, Italy and the Study Director is responsible for the selection of the study sites. Any center performing emergency surgery can participate in this trial. The centers include academic medical centers, teaching hospitals, tertiary referral centers and community hospitals. Although this study protocol is similar to what adopted in previous research (26), in order to ensure that there is a uniformity of data acquisition, centers which do not participated in such previous study performed a 3-month pilot study collecting data retrospectively. All the data taken refers to the time of access of the patient in the emergency room or in any case to the first data available before any procedure. Such data are not published, and are stored separately for possible further analyses. All patients are treated according to the local hospital protocol and receive routine care as standard therapy. Whenever possible, patients with intestinal obstruction are treated according to SICUT Delphi consensus statements (27). The duration of the recruitment phase of patients is expected to be 18 months. The main strength of this project is the multicenter, prospective, contemporary methodology, with independent validation of data. This will produce high quality data on the emergency procedures carried out for gastro-intestinal emergency and on outcomes throughout Italy from a wide range of hospital types. Limitations include the inability to assess the postoperative visits to the general practitioner. Moreover, a minority of patients may present to other hospitals with complications following surgery, or because they need medical assessment. Despite this, teams will try to document the number of patients that were readmitted to other facilities. Our study uses the standard 30-day follow-up period, as this is the international standard and allows comparison to other studies. However, complications which may occur after 90 days will be reported as completely as possible.

## Trial population recruitment and eligibility criteria

### Inclusion criteria

All patients over the age of 18, undergoing urgent/emergency abdominal surgery will be included in the study. Emergency procedures are defined as unforeseen, non-elective operations according to the NCEPOD Classification of Interventions (28). The type of surgical approach takes into account open abdominal or laparoscopic procedures, including laparoscopic procedures that are converted to open abdominal procedures. Surgical procedures will be sorted on the basis of the 9th revision of International Classification of Disease Clinical Modification (ICD-9-CM). All abdominal procedures with ICD-9-CM code numbers ranging from 42.0 to 54.99 are considered eligible.

### Exclusion criteria

Exclusion criteria include any patient under 18 years at the day of surgery; lack of informed consent; patients already hospitalized and scheduled for the same procedure; participation in another trial.

### Outcome measures

The primary outcomes are 30-day overall postoperative morbidity and mortality rates. Secondary outcomes are 30-day postoperative morbidity and mortality rates, stratified for each procedure or cause of intervention, length of hospital stay, admission and length of stay in ICU, and place of discharge (home or rehabilitation or care facility). Severity of every disease will be assessed according to the AAST EGS score (29). Other secondary outcomes include the number of elderly subjects undergoing yearly emergency surgery, reported as the elderly to non-elderly patient ratio, emergency surgery in the elderly per 100,000 inhabitants, frequency of use of frailty score. Elderly are define as any patient >65 years old according to the World Health Organization. Moreover, the study will evaluate the sensitivity and specificity of the following scores: Charlson Age Comorbidity Index (CACI), Simplified Acute Physiology Score II (SAPSII), American College of Surgeons National Surgical Quality Improvement Program (ACS NSQIP), Calculation of Postoperative Risk in Emergency Surgery (CORES), Surgical Mortality Probability Model (SMPM), Urgent Surgery Elderly Mortality (USEM) score, Emergency Surgery Frailty index (EmSFI), 5 modified Frailty Index (5-mFI). The postoperative complications are reported and categorized according to the Clavien-Dindo classification system. Morbidity we will be assessed by detecting all adverse event according “Common terminology criteria for adverse events version 5” (30). Therefore, the Comprehensive Complication Index will be calculated (31).

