### Data collection, validation, and management

In each participating hospital, one local investigator (usually a surgical resident/student) is responsible for data collection and for entering data into a password-protected electronic spreadsheet specifically constructed with predefined data fields. There are six categories, namely “patient demographics”, “comorbidities”, “clinicopathological data”, “surgical intervention”, “score”, and “follow-ups” (Table 1). Patient details will be recorded and anonymized using the code centre, an ID number and a unique alphanumeric code for any further integration. The anonymization procedure is provided by the enrolling centre. Patient data will be collected, if possible, on a daily basis; preoperative and intraoperative data will be processed after surgery, and the postoperative outcomes will be noted at the time of discharge and at the end of follow-ups. Data will be obtained from the electronic patient database, from admission charts, and operative reports, or directly from the surgeon who performed the operation when details were unclear or missing. Consent to participate in the study and to collect data for scientific purpose will be obtained from the patient at admission. The standardized data collection protocol has been approved by the Central Ethical Committee. There is no minimum number of patients per centre. Following data collection, only datasets with >95% data completeness will be accepted for pooled national analysis. The principal investigator (PI) at the selected site will identify an independent assessor to validate all data, with a target of >98% accuracy. Overall, at least 5% of the datasets will be independently validated. Outcome data will not be analyzed specific to each individual center. Data will be submitted monthly *via* e-mail or inserted in an online module. Once in the Data Coordination Centre (DCC) pooled warehouse, records are reviewed and edited and, whenever necessary, transformed to comply with the GESEMM data dictionary (see Table 1 for further information). The Study Director and the Study Coordinator will then identify unacceptable data entries using custom software queries to detect missing, impossible and improbable values and logical inconsistencies between data fields and across the forms. The DCC will then ask the sites to check for the incomplete data, and once the sites have resolved the data queries, the DCC will update the patient records. To identify complications during follow-up, each center will check their database to monitor visits to the emergency department, postoperative imaging or intervention, outpatient visits or hospital readmissions. Additional checking of admission diagnosis and surgical procedures in the study months will identify any missing patients. The data will be collected from each individual center according to the current Italian Law regarding privacy policy (Legislative Decree no. 196/2003 “RIGHT TO PERSONAL DATA PROTECTION CODE”). It will be the responsibility of the local investigators to ensure that the local data will be protected and held according to such privacy policy and in line with what has been approved by the ethics board. No patients are involved in setting the research question or the outcome measures; nor are they involved in the design and implementation of the study. There are no plans to involve patients in dissemination of results.

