	Onset symptoms	Obstruction, acute abdomen (peritonitis—abscess and/or overt perforations), Vascular disorders, Trauma
	Primary operative indication	Benign/malignant/delayed elective
	Surgical approach	Open/Laparoscopic/Laparoscopic converted/Laparoscopic assisted
	Primary surgical procedure	ICD-9-CM code
	Associated procedures	Numbers
	List of associated procedures	ICD-9-CM code
	Intraoperative reliefs	Blood loss (ml), peritoneal contamination (yes/no)
	Operative time	Minutes
	ICU admission	Yes/no
	ICU length of stay	Dayes
Follow-ups	Date of discharge	Day/month/year
	Total length of stay	Days
	Type of discharge	Home, short-term rehabilitation facility, caregiver residential facility
	Complications 30-daypostoperatively	Yes/no
	Complication type	Free text
	Complication grade (Clavien-Dindo classification)	None/I/II/III/IV/V
	30-day mortality	Yes/no
Score		ASA, CACI, SAPSII, ACS-NSQIP, CORES, SMPM, USEM, EmSFI, 5-mFI

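### The follow-up fields in Table 1 record no a/b sub-grades and no grade for each complication, so they do not support the Comprehensive Complication Index for any grade III or IV or for several non-fatal complications

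*Protocol article*

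**What the plan says.** Under Outcome measures, the protocol article makes three linked statements. Complications are graded: "The postoperative complications are reported and categorized according to the Clavien-Dindo classification system". All events count: "Morbidity we will be assessed by detecting all adverse event", using CTCAE version 5. The index follows from this: "Therefore, the Comprehensive Complication Index will be calculated". Expected results names the index again, in a list of scores to be evaluated for sensitivity and specificity.

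Under Data collection, validation, and management, data go into a "password-protected electronic spreadsheet specifically constructed with predefined data fields". Pooled records are transformed to fit the study's data dictionary, for which the reader is sent to Table 1. The Follow-ups rows of that table give a yes/no field for 30-day complications, a free-text field labelled "Complication type", one Clavien-Dindo grade field with the options "None/I/II/III/IV/V", and a yes/no field for 30-day mortality. Neither the Follow-ups rows nor the Score row lists the index.

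**The concern.** A cumulative complication index is meant to reflect every complication a patient has, weighted by severity. That is what separates it from the highest Clavien-Dindo grade. The plan ties the index to the detection of all adverse events, but the listed fields offer one grade and merge the a and b levels of grades III and IV.

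If the index were computed from these fields as printed, it would be a recoding of one grade, with a chosen weight for every III and IV. It would add nothing to Clavien-Dindo in the patients for whom a cumulative measure is intended, those with several or severe non-fatal complications. Two analysts could also obtain different values from the same record.

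**Working it through.** The article gives no value, formula or weights for the index, so there is no figure to reproduce. The check has two parts.

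**1. Required items against listed fields**

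| Needed for a cumulative index | Listed in Table 1, Follow-ups |
|---|---|
| A grade for each complication | One grade field |
| IIIa or IIIb, IVa or IVb | III and IV only |
| Number of complications | Not listed; free text may name several |
| Death | 30-day mortality yes/no, and grade V |

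Two features of Table 1 suggest that the grade field is meant per patient. The option None has little use in a form with one row per event. For procedures, where multiplicity is intended, the table has a primary code, a number of associated procedures and a list of their codes; complications have no equivalent.

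**2. Size of the error, for illustration**

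Assumptions, none of them in the documents: index = √(sum of weights over all complications) / 2, with grade V set to 100; weights I 300, II 1750, IIIa 2750, IIIb 4550, IVa 7200, IVb 8550.

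Single complications: I 8.7; II 20.9; IIIa √2750/2 = 26.2; IIIb √4550/2 = 33.7; IVa √7200/2 = 42.4; IVb √8550/2 = 46.2. Losing the sub-grade alone thus leaves a lone III at 26.2 or 33.7, and a lone IV at 42.4 or 46.2.

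| True complications | Full index | From highest grade only |
|---|---|---|
| II+II | √3500/2 = 29.6 | 20.9 |
| II+II+II | √5250/2 = 36.2 | 20.9 |
| IIIb+II+II | √8050/2 = 44.9 | 26.2 or 33.7 |
| IVa+II+II | √10700/2 = 51.7 | 42.4 or 46.2 |
| II+IIIb+IVa | √13500/2 = 58.1 | 42.4 or 46.2 |
| IIIa+I | √3050/2 = 27.6 | 26.2 or 33.7 |
| IVa+I | √7500/2 = 43.3 | 42.4 or 46.2 |

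For II+IIIb+IVa the shortfall is 58.1 − 46.2 = 11.9 to 58.1 − 42.4 = 15.7 points. For three grade II events it is 36.2 − 20.9 = 15.3.

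Over all combinations of non-fatal grades, with the correct sub-grade of the worst complication known, the shortfall is 0.8 to 19.2 points for two complications and 1.6 to 33.8 for three. Where the sub-grade must be guessed, the single-grade value can exceed the true one in 3 of 21 two-complication combinations and 2 of 56 three-complication combinations. The last two rows of the table show this: 33.7 against 27.6, and 46.2 against 43.3. These are counts of combinations, not of patients. With grade V the index is 100 either way.

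**The case against.** The strongest reply is that Table 1 is a condensed list. One row can stand for many cells (the vital parameters row covers nine items), and other planned items, such as the AAST severity score and the CTCAE coding, have no row at all. The table does not say that the grade field takes one entry, holds the worst grade or cannot repeat. This stands: one grade per patient is a strong inference, not a stated fact. It does not reach the sub-grades, because the option list is printed in full and stops at III and IV.

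The second reply is recovery. The data section allows recourse to charts, operative reports or the surgeon when details are unclear or missing, and the time-line keeps 1 March to 30 June 2023 for completing missing data. So the grades are not irrecoverably lost. As described, however, these steps serve the predefined fields. A patient with three complications and one grade IV has a complete and consistent record, so the planned checks for missing or contradictory entries would raise no query.

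A reader might go further and infer that the index cannot be computed at all, or that every reported value will be too low. The documents do not support either. The index is determinable for some patients, and a guessed sub-grade can push it upward. A reader might also take the Discussion's statement that about half of patients develop a complication as the share affected. That figure concerns any complication; the article does not say how many patients have several, or how many reach grade III or IV.

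**Conclusion.** The concern holds in a limited form. As listed, the follow-up fields leave the index ambiguous for any grade III or IV and not derivable for patients with several non-fatal complications. It can be derived for patients with no complication, with a single grade I or II (provided the free text shows there was only one), or with grade V.

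Under the assumed weights, relying on the highest grade usually understates the index, by roughly 12 to 16 points in the three-complication example with grade IVa, and can occasionally overstate it. The direction and size rest on the outside formula and weights. The fact that sub-grades are missing rests only on the printed option list. The number of patients affected cannot be estimated from the article.

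The primary outcomes, the 30-day morbidity and mortality rates, have their own yes/no fields and are unaffected. The index is not in the article's enumerated lists of primary or secondary outcomes. This is worth correcting because the plan commits to the index and the correction is small.

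**What to change.** Change the follow-up form so that each complication is entered separately with its type and full Clavien-Dindo grade (I, II, IIIa, IIIb, IVa, IVb, V). Have the Data Coordination Center compute the index from these entries, and state the formula and weights used.

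For records already closed with one grade, use the planned missing-data completion period to obtain the individual grades wherever the free text names several complications or the grade is III or IV. Its scope should be widened explicitly to cover this, since such records would not be flagged as incomplete. If this is not done, report the highest Clavien-Dindo grade instead of the index.

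The cost is a spreadsheet change, a few more entries for patients with complications, and some chart work for records already closed. No extra visits are needed. Dropping the index in favour of the highest grade requires no further data collection.

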### Data collection, validation, and management

In each participating hospital, one local investigator (usually a surgical resident/student) is responsible for data collection and for entering data into a password-protected electronic spreadsheet specifically constructed with predefined data fields. There are six categories, namely “patient demographics”, “comorbidities”, “clinicopathological data”, “surgical intervention”, “score”, and “follow-ups” (Table 1). Patient details will be recorded and anonymized using the code centre, an ID number and a unique alphanumeric code for any further integration. The anonymization procedure is provided by the enrolling centre. Patient data will be collected, if possible, on a daily basis; preoperative and intraoperative data will be processed after surgery, and the postoperative outcomes will be noted at the time of discharge and at the end of follow-ups. Data will be obtained from the electronic patient database, from admission charts, and operative reports, or directly from the surgeon who performed the operation when details were unclear or missing. Consent to participate in the study and to collect data for scientific purpose will be obtained from the patient at admission. The standardized data collection protocol has been approved by the Central Ethical Committee. There is no minimum number of patients per centre. Following data collection, only datasets with >95% data completeness will be accepted for pooled national analysis. The principal investigator (PI) at the selected site will identify an independent assessor to validate all data, with a target of >98% accuracy. Overall, at least 5% of the datasets will be independently validated. Outcome data will not be analyzed specific to each individual center. Data will be submitted monthly *via* e-mail or inserted in an online module. Once in the Data Coordination Centre (DCC) pooled warehouse, records are reviewed and edited and, whenever necessary, transformed to comply with the GESEMM data dictionary (see Table 1 for further information). The Study Director and the Study Coordinator will then identify unacceptable data entries using custom software queries to detect missing, impossible and improbable values and logical inconsistencies between data fields and across the forms. The DCC will then ask the sites to check for the incomplete data, and once the sites have resolved the data queries, the DCC will update the patient records. To identify complications during follow-up, each center will check their database to monitor visits to the emergency department, postoperative imaging or intervention, outpatient visits or hospital readmissions. Additional checking of admission diagnosis and surgical procedures in the study months will identify any missing patients. The data will be collected from each individual center according to the current Italian Law regarding privacy policy (Legislative Decree no. 196/2003 “RIGHT TO PERSONAL DATA PROTECTION CODE”). It will be the responsibility of the local investigators to ensure that the local data will be protected and held according to such privacy policy and in line with what has been approved by the ethics board. No patients are involved in setting the research question or the outcome measures; nor are they involved in the design and implementation of the study. There are no plans to involve patients in dissemination of results.

**Table 1 T1:** Data spreadsheet fields: ASA American society of anaesthesiologists, BMI body mass index, BUN blood urea nitrogen, CPAP continuous positive airway pressure, CRP C-reactive protein, GCS glasgow coma scale, ICD-9-CM 9th revision of international classification of disease clinical modification, ID identifier, INR international normalized ratio, MI myocardial infarction, mFI modified frailty Index, PCI percutaneous coronary intervention, PLT platelet, WBC white blood cell, P-POSSUM portsmouth-physiological and operative severity score for the enUmeration of mortality and morbidity, CR-POSSUM coloRectal physiological and operative severity score for the enUmeration of mortality and morbidity, SAPS II simplified acute physiology score II, CACI charlson age-comorbidity index, EmSFI emergency surgical frailty index.

Form	Field	Options (definitions)
Demographics	ID	Progressive number
	ID center	Number
	ID code	Alphanumeric (3 characters)
	Age	In years
	Sex	Male/Female
	BMI	BMI in kg/m^2^
	Admission date	Day/month/year
	Operation date	Day/month/year
	Timing of surgery	Emergency/urgency
Clinicopathological data	Vital parameters	Systolic blood pressure, heart rate, respiratory rate, oxygen saturation, temperature, urine output, mechanical ventilation or CPAP, FiO2, GCS
	Laboratory analysis	Arterial blood gas analysis (PaO2, PaCO2 bicarbonate, lactates), chemistry (sodium, potassium, bilirubin, glycemia, CRP), renal function (BUN, creatinine), hemoglobin, WBC, PLT, INR
	Tumor	Site, TNM classification, Dukes staging system, grading, radicality of surgery, vascular invasion
Comorbidities	Associated diseases	Cardiovascular disease (ECG-report, hypertension, MI < 6 months, heart failure <30 days, chronic heart disease, Previous cardiac surgery or PCI, peripheral vasculopathy), cerebrovascular disease, respiratory disease (chronic lung diseases, respiratory failure), smoke, renal disease (acute/chronic), diabetes, liver disease (acute/chronic), solid tumor (localized/metastatic) leukemia, lymphoma, AIDS, drugs (oral anticoagulants, immunosuppressants or steroids, oral hypoglycemic agents or insulin), peptic ulcer
	Performance status	Hemiplegia, dementia, weight loss, physical activity, walk time, grip strength, exhaustion
Surgical intervention	Organ/body-district categories	Abdominal wall, appendicitis, biliary tract and pancreas, esophagus, large bowel, small bowel, solid organs, stomach and duodenum, thorax, Others
	Onset symptoms	Obstruction, acute abdomen (peritonitis—abscess and/or overt perforations), Vascular disorders, Trauma
	Primary operative indication	Benign/malignant/delayed elective
	Surgical approach	Open/Laparoscopic/Laparoscopic converted/Laparoscopic assisted
	Primary surgical procedure	ICD-9-CM code
	Associated procedures	Numbers
	List of associated procedures	ICD-9-CM code
	Intraoperative reliefs	Blood loss (ml), peritoneal contamination (yes/no)
	Operative time	Minutes
	ICU admission	Yes/no
	ICU length of stay	Dayes
Follow-ups	Date of discharge	Day/month/year
	Total length of stay	Days
	Type of discharge	Home, short-term rehabilitation facility, caregiver residential facility
	Complications 30-daypostoperatively	Yes/no
	Complication type	Free text
	Complication grade (Clavien-Dindo classification)	None/I/II/III/IV/V
	30-day mortality	Yes/no
Score		ASA, CACI, SAPSII, ACS-NSQIP, CORES, SMPM, USEM, EmSFI, 5-mFI

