### Study time-line

The following timeline has been outlined, to define specific stages of the study:
•May 13–June 30, 2021: invitation to satellite centers to participate.•1 July–31 August, 2021: pilot study and standardization of data collection.•1 September 2021–31 August, 2022: main data collection.•1 September 2022–28 February, 2023: data collection on specific topics.•1 March–30 June, 2023: completion of the collection of any missing data.•1 July–31 December 2023: “interim analysis” of complete data excluding follow-up•February 28, 2025: study completion for last potential follow-up.

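### Missing predictors and scores may be completed after the 30-day outcome is known, so the comparison of score accuracy may be biased by an unknown amount

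*Protocol article*

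**What the plan says.** All references are to the protocol article.

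- **Who records.** Under Data collection, validation, and management, in each hospital "one local investigator (usually a surgical resident/student) is responsible for data collection and for entering data into a password-protected electronic spreadsheet". The spreadsheet has six categories, and both the score form and the follow-up form are among them.
- **When.** "Patient data will be collected, if possible, on a daily basis". The order of entry is then fixed: "preoperative and intraoperative data will be processed after surgery, and the postoperative outcomes will be noted at the time of discharge", with a second recording of outcomes once follow-up closes.
- **From what source.** Charts, operative reports and the electronic database come first. The surgeon is the fallback, since details may be taken "directly from the surgeon who performed the operation when details were unclear or missing".
- **Pressure to fill gaps.** The same section accepts only datasets with more than 95% completeness for the pooled analysis, and the Data Coordination Centre (DCC) returns incomplete records to sites.
- **Late window.** The Study time-line sets 1 March to 30 June 2023 for "completion of the collection of any missing data".
- **What is recorded.** The score row of Table 1 lists "ASA, CACI, SAPSII, ACS-NSQIP, CORES, SMPM, USEM, EmSFI, 5-mFI". The performance-status row includes dementia, weight loss, physical activity and exhaustion.
- **What it is used for.** Objectives seeks the most suitable existing score and variables for a new one. Outcome measures names eight scores for sensitivity and specificity. Statistical analysis plans ROC curves for each score.

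**The concern.** A fair estimate of prognostic accuracy needs the predictor to be settled without knowledge of the outcome. The gap-filling rules do not secure this. They allow a missing baseline item to be completed months after the operation, by someone who may also be recording the outcome or by the surgeon who treated the patient.

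For a laboratory value copied from a dated report this matters little. For an item that needs judgement or recall, such as dementia, weight loss, physical activity or exhaustion, knowing that the patient died or had a complication can influence the entry. If it does, that item, and any score using it, will look more predictive than it would at the bedside. At stake are the comparison of existing scores and the choice of variables for a new one.

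**Working it through.** The article states no sample size, expected accuracy or back-filled share, so there is no figure of its own to reproduce. Two checks apply.

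**1. Dates.** Inputs from Study time-line: main collection 1 September 2021 to 31 August 2022; specific-topic collection 1 September 2022 to 28 February 2023; completion of missing data 1 March to 30 June 2023. Input from Outcome measures: 30-day horizon.

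- Last main-phase operation: 31 August 2022 + 30 days = 30 September 2022, which is 152 days before the window opens.
- Last second-phase operation: 28 February 2023 + 30 days = 30 March 2023, which is 92 days before the window closes.
- Latest operation date reaching day 30 by 1 March 2023: 30 January 2023. From 1 September 2021 that covers 517 of the 546 days in the 18 months: 517 / 546 = 0.947.

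A predictor completed in this window is therefore almost always completed after the 30-day outcome has occurred. The 95% is a share of calendar days. It equals a share of patients only if operations are spread evenly.

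**2. Direction and possible size.** Everything in this step is an assumption: binormal score, true AUC 0.75, share m of scores back-filled.

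Separation: d = √2 × Φ⁻¹(0.75) = 1.414 × 0.6745 = 0.954.

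*Outcome-driven entry*: back-filled scores of event patients move up by s SD.

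AUC = (1 − m) × 0.75 + m × Φ((d + s)/√2)

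- s = 0.25: Φ(1.204/1.414) = 0.803
- s = 0.5: Φ(1.454/1.414) = 0.848
- Example, m = 0.20, s = 0.5: 0.80 × 0.75 + 0.20 × 0.848 = 0.770

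*Random recall error*: noise of t SD is added to back-filled scores in event and non-event patients alike.

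AUC = (1 − m)² × 0.75 + 2m(1 − m) × Φ(d/√(2 + t²)) + m² × Φ(d/√(2 + 2t²))

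- Example, m = 0.20, t = 1: 0.64 × 0.75 + 0.32 × 0.709 + 0.04 × 0.683 = 0.734

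| Share back-filled | Outcome-driven, s = 0.25 to 0.5 | Random error, t = 0.5 to 1.0 |
|---|---|---|
| 5% | 0.753 to 0.755 | 0.749 to 0.746 |
| 10% | 0.755 to 0.760 | 0.748 to 0.742 |
| 20% | 0.761 to 0.770 | 0.745 to 0.734 |

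Against 0.75, the change runs from about +0.003 to +0.020 in one case and −0.001 to −0.016 in the other. The 95% completeness rule does not bound m, because it is applied after gaps have been filled.

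**The case against.** The other side has a good deal of substance.

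- **The planned order is right.** The sentence on processing puts preoperative data before outcomes and aims at daily collection. Processing after surgery need not mean after a 30-day outcome. A reader might infer from it that predictors are routinely recorded with the outcome known; it does not say so. The exposure lies in late completion only.
- **One responsible person is not one pair of hands.** Study design and participating sites describes teams with senior oversight. Being responsible for both forms permits overlap but does not prove it.
- **There are safeguards.** The same section says values refer to emergency-room access or the first data before any procedure. Charts are the main source. An independent assessor has a target above 98% accuracy, with at least 5% of datasets validated. These reduce the risk without removing it. The time-point sentence stands between two sentences on the retrospective pilot, so its scope is unclear, and it fixes the moment a value refers to, not what the person entering it knows. Checking entries against records need not reveal a judgement coloured by the outcome.
- **The completion window is general.** It covers any missing data and does not single out predictors. It does not exclude them either.
- **Which scores are exposed is not shown.** No section gives the components of any score, and ASA, though listed in Table 1, is not among the eight scores to be evaluated. A firm split into subjective and laboratory-based scores is therefore not available. The candidate variables for a new score are exposed whatever score they belong to.
- **Some details belong elsewhere.** Date stamps, form locks and whether score totals are typed in or computed may be settled in the full protocol. Their absence from an article is no fault.

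**Conclusion.** The point holds as a risk of bias. The stated rules let predictors and scores be completed after the 30-day outcome is known, in a study that sets out to compare score accuracy.

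A reader might go further and conclude that accuracy is inflated, or that the ranking of scores will be reversed. The documents do not support that. Inflation requires entries to be driven by the outcome, while random recall error pulls the other way. A change of rank also requires two scores to be affected unequally. Upward bias is the more plausible direction for judgement items, but that is a judgement and not a result.

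A reader might also take the longest gap, 22 months from 1 September 2021 to 30 June 2023, as typical. It applies only to a first-day patient whose gap is closed on the last day.

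The size is unknown. The apparent AUC of 0.734 to 0.770 around 0.75 rests wholly on the assumed shares, shifts and noise. Changes of that order matter only between scores of similar accuracy. The primary 30-day morbidity and mortality rates are untouched. This is an inexpensive improvement to the score evaluation and not a threat to the study's main result.

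**What to change.** Amend the data-completion rules as follows:

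1. For predictors, limit query resolution and the March to June 2023 completion to values documented in the record before the operation.
2. Flag any predictor or score completed after the outcome has occurred.
3. Have the DCC calculate, without sight of outcomes, every score that can be computed from the raw Table 1 fields.
4. Repeat the ROC comparison without flagged values and report both results, with the number of flagged values per score.

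If the full protocol already contains such rules, a sentence in the article would be enough.

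The cost is one flag, central calculation from data already collected and one further analysis. The downside is a few more missing subjective items, some of which could count against the 95% completeness threshold, so the plan should say how they are treated there.
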